#### Secondary Outcomes

Data on several secondary outcomes will be collected (Table 2). These include adverse events and complications during treatment and recovery, cost-effectiveness–relevant outcomes such as hospital stay duration and use of (co)medication, patient-reported experiences, reintervention rate in case a uterine-sparing treatment was performed, reproductive outcomes when applicable, and technical outcomes after MR-HIFU, such as NPV reached.

**Table 2 table2:** Secondary outcomes of the MYCHOICE^a^ study, including measurement tool and statistical analyses.

Outcome	Description	Measurement	Statistical analyses
QoL^b^ parameters	QoL is expected to be negatively correlated with symptom severity. When symptoms decrease, the QoL is expected to improve.	UFS-QoL^c^ questionnaire and EQ-5D-5L^d^ questionnaire.	The time course of the change in health-related quality of life after treatment will be analyzed using longitudinal covariance analysis similar to the analysis of the change in SSS^e^.
Adverse events and complications	The nature of adverse events and complications of the 2 treatment arms are expected to differ.	Adverse events will be classified according to the classification of surgical complications [32].	Adverse events are analyzed using descriptive statistics. Adverse events per treatment group and treatment will be presented with their occurrence rate.
Length of hospital stay	Reduced hospital stay is beneficial in terms of health care costs and is also considered as a great advantage by patients.	Length of hospital stay will be collected from the patient hospital file.	The average length of the hospital stay will be reported as mean (SD) or median (interquartile range).
Periprocedural and postprocedural pain	Pain perception may influence treatment experience and therefore satisfaction with the treatment.	Periprocedural and postprocedural pain will be measured on a numerical rating scale from 0 to 10 in the 3 months’ follow-up questionnaire. Pain complaints at 3, 6, 12, and 24 months after treatment will be registered by the amount and duration of pain killers used.	The numerical rating score is considered to be a semicontinuous measure (range 0-10: higher score represents more pain). Pain experienced will be reported as mean (SD) or median interquartile range.
Patient-reported satisfaction with treatment and treatment preference (PREM^f^)	Because a randomized controlled trial will be performed, satisfaction with treatment might be affected by not being allocated to preferred treatment. Furthermore, we expect women declining participation because of the randomization aspect of the trial.	The PREM consists of a concise set of statements about the experience of the patients with the treatment and whether they would recommend the treatment to a friend. In addition, the preference will be registered for a particular treatment of potential participants before randomization. Women who decline participation in the study will also be asked if they are willing to disclose their reasons for declining.	The PREM score is scored on a 5-point Likert scale: higher score represents better experience. Whether there is a difference in PREM outcome between the 2 treatment arms is determined by linear regression analysis.
(Co)medication	Women (still) experiencing symptoms after treatment may take or may start to take medication to relieve these symptoms. Medication might also be used as contraceptive and to mask possible fibroid-related symptoms at the same time.	Data on any prescribed or over-the-counter medication taken to reduce fibroid symptoms as reported by the patient will be collected via the questionnaires at baseline, 3, 6, 12, and 24 months after treatment.	The number of women taking medication to suppress fibroid-related symptoms is measured at baseline and 3, 6, 12, and 24 months after treatment. The absolute numbers and percentage of women taking comedication per group per time point will be presented.
Reintervention rate and time to reintervention	A reintervention is defined as an additional intervention due to persisting or recurring symptoms of the treated fibroid or due to complications of the initial fibroid treatment.	Occurrence and type of reintervention are collected via both electronic patient file and questionnaires at 3-, 6-, 12-, and 24-month follow-up.	The reintervention rate at the follow-up time point of 24 months after MR-HIFU^g^ is presented as percentage reinterventions with its 95% CI. Reintervention rate will be presented per treatment arm but also per treatment. To investigate whether the time to reintervention differs between the 2 treatment arms, Cox proportional hazards analysis will be used.
Onset of menopause after uterus-saving treatments	Uterine fibroid symptoms diminish after menopause along with fibroid-related symptoms. Because this may affect symptom reduction, QoL, and the possible need for a reintervention, the menopausal state of the participants will be determined.	Onset of menopause is defined as 1 year without menstrual bleeding and measured by a questionnaire at the 24-month follow-up.	The absolute numbers and percentage of postmenopausal women per group and treatment will be presented.
Reproductive outcomes after uterus-saving treatments	Only women with an active wish to conceive within 1 year after treatment will be excluded from this study. Thus, some women may get pregnant after the uterus-saving treatment.	Reproductive outcomes will be collected of all women that underwent a uterus-saving treatment by a questionnaire at 24-month follow-up.	Reproductive outcomes will be presented per uterus-saving group using absolute numbers and percentage.
NPV^h^ and fibroid shrinkage after MR-HIFU treatment	Technical success of MR-HIFU is commonly presented as NPV percentage directly after treatment or fibroid shrinkage 6 months after treatment, as determined on an MRI^i^ scan.	NPV% will be measured on an MRI scan performed directly after treatment. Fibroid shrinkage will be measured by comparing volume measured on 6 months’ follow-up MRI scan with pretreatment volume.	We will investigate whether technical success (NPV% [NPV/initial volume of the fibroid] or fibroid shrinkage) is associated with (long-term) effectiveness using regression analysis.
Other study parameters	Several patient characteristics are collected from the medical record of the patients and from the baseline questionnaire such as age, amount and size of fibroids, location of fibroid, position of uterus, duration of treatment, ethnicity, parity, height, weight, relevant medical, and medical history.	Data analysis will be stratified by center to check for differences in results between centers.	In case necessary, multilevel analysis will be used to correct for differences between centers. Multivariate analysis will be performed for symptom reduction, QoL improvement, and reintervention correcting for comedication or menopause as possible confounder. In addition, we will investigate whether certain baseline characteristics such as age, BMI, number of uterine fibroids, and target fibroid size are associated with symptom reduction and reintervention using linear, logistic, and Cox regression analysis.

^a^MYCHOICE: MYoma treatment Comparison study: High-intensity image–guided fOcused ultrasound versus standard (minimally) Invasive fibroid care—a (Cost-)Effectiveness analysis.

^b^QoL: quality of life.

^c^UFS-QoL: Uterine Fibroid Symptom and Quality of Life questionnaire.

^d^EQ-5D-5L: 5-level version of the EuroQoL questionnaire.

^e^SSS: symptom severity score.

^f^PREM: patient-reported experience measurement.

^g^MR-HIFU: magnetic resonance image–guided high-intensity focused ultrasound.

^h^NPV: nonperfused volume.

^i^MRI: magnetic resonance imaging.

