## Introduction

Fibroids are the most common benign gynecological tumors in women of reproductive age, occurring in up to 70% of the population. Approximately 25% of the uterine fibroids are symptomatic [1]. Symptoms include abdominal pain, menstrual disorders, lower urinary tract or bowel symptoms, and fertility disorders [2]. On a global level, fibroids represent an enormous economic burden to the health care system and costs can reach as much as US $5.9-34.4 billion each year in the United States [3]. Conservative treatment of fibroids fails in 50% of patients, many of whom subsequently opt for surgical procedures [4]. Hysterectomy is currently the most common treatment for symptomatic uterine fibroids, with millions of procedures performed annually around the world [5]. However, hysterectomies and myomectomies have a high risk of complications, long recovery, and might compromise future pregnancies [6], with the latter mainly due to peritoneal and intrauterine adhesions, a high rate of abnormal placentation, and fragility of myometrium as a result of myomectomy [7]. Furthermore, even a hysterectomy does not guarantee an intervention-free life, mostly because of complications caused by the operation itself [8]. This has led to a strong desire for less invasive treatments [4].

Currently, uterine artery embolization (UAE) is the only reimbursed minimally invasive treatment available in the Netherlands. The general treatment results after UAE are 60% fibroid volume reduction and on average 80%-90% patient satisfaction [9]. Complications after UAE include nontarget embolization, infection/septicemia and ovarian failure due to impairment of ovarian blood flow, and infection leading to fallopian tube damage with subsequent infertility [9,10].

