#### Control Group

The care as usual group will be offered surgery or UAE. Surgery will be either hysterectomy or myomectomy. Both hysterectomies and myomectomies can be performed by laparoscopy or laparotomy depending on the size and location of the fibroids. Participants allocated to the control group can decide together with their gynecologist which of the (minimally) invasive treatments they wish to undergo. All of the usual care treatments are performed extensively at the participating centers and will be performed according to national guidelines and local protocols. Surgery is preceded by a preoperative screening for anesthetic risk assessment. Depending on the modus of the hysterectomy or myomectomy, patients will be hospitalized for a minimum of 1-3 nights. UAE will be performed by well-trained and experienced radiologists. UAE can be either unilateral or bilateral. The patient usually has to stay in the hospital for 1-3 nights for careful pain monitoring after the procedure. Six weeks after all usual care treatments, a follow-up appointment at the gynecology department will be scheduled.

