### Strengths

As a primary outcome, we will use QoL in terms of symptom reduction 24 months after treatment. We did not choose the commonly used outcome in uterine fibroids studies, reintervention rate, as our primary outcome because re-interventions are not expected to occur after hysterectomy. Symptom reduction will most likely also differ between hysterectomy and uterus-saving treatment options. However, the influence of symptom reduction after hysterectomies in the control group is probably limited, because we expect that most women who will participate in the MYCHOICE study prefer a uterus-preserving treatment option, just like the intervention under study. This is further enhanced by the 2:1 randomization ratio. This ratio will lead to a higher chance to undergo MR-HIFU treatment, and we believe is therefore an important strength of the design. Another strength is the fact that this unbalanced design will enable us to gather more data on our intervention, while the effectiveness of standard care is already much better documented.

Our follow-up duration of 24 months is based on the long-term outcomes of a retrospective study on MR-HIFU treatment results performed by our group [14]. In this study, we found that all reinterventions were performed within 24 months after the initial treatment, indicating that the treatment effect reaches a steady state within 24 months after treatment. Thus, it is not useful to prolong follow-up of these patients.

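### The text limits the reintervention outcome to uterine-sparing treatments while Table 2 compares the randomized arms, so the analysis set is contradictory and one of its two versions is not a randomized comparison

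*Protocol article*

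**What the plan says.** The opening paragraph of Secondary Outcomes in the protocol article names the outcome as "reintervention rate in case a uterine-sparing treatment was performed".

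The reintervention row of Table 2, in the same section, carries no such condition. Its definition, shortened here at the end, reads "A reintervention is defined as an additional intervention due to persisting or recurring symptoms of the treated fibroid or due to complications of the initial". On reporting it says "Reintervention rate will be presented per treatment arm but also per treatment". On testing it says "To investigate whether the time to reintervention differs between the 2 treatment arms, Cox proportional hazards analysis will be used".

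Statistical Methods states that the data are first analyzed by intention to treat, with a per-protocol analysis in addition.

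The Control Group section sets out the comparator: "The care as usual group will be offered surgery or UAE. Surgery will be either hysterectomy or myomectomy". It adds that the choice is made once the allocation is known: "Participants allocated to the control group can decide together with their gynecologist which of the (minimally) invasive treatments they wish to undergo".

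On reinterventions after hysterectomy, the Strengths section says "re-interventions are not expected to occur after hysterectomy", while the Introduction says "even a hysterectomy does not guarantee an intervention-free life, mostly because of complications caused by the operation itself".

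**The concern.** A restriction to uterine-sparing treatments and a comparison of randomized arms cannot both govern the same analysis. Every woman treated as planned in the MR-HIFU arm meets the restriction. In the control arm, women who choose hysterectomy do not. Because they choose after randomization, leaving them out conditions one arm on a post-randomization decision. What remains is a self-selected part of the control arm set against the whole MR-HIFU arm.

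The restriction also sits badly with the Table 2 definition. A procedure for a complication of hysterectomy qualifies as a reintervention there, but the Secondary Outcomes text would leave it out.

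At stake is the meaning of the arm-level reintervention rate and of the hazard ratio. The Strengths section itself calls reintervention rate the outcome commonly used in fibroid studies, so readers will look at this result closely.

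**Working it through.** **Plan's own figures.** The protocol gives no calculation, event rate or hysterectomy share for reintervention. Its only calculated figure is the primary sample size, which reproduces. With a margin of 15, an assumed difference of 5, SD 20, one-sided alpha 0.025, power 0.90 and 2:1 allocation, the control group needs 1.5 × (20 × (1.960 + 1.282) / 10)² = 63.04, rounded up to 64. That gives 128 for MR-HIFU and 192 in total; dividing by 0.8 for dropout gives 80 and 160. This point does not affect any of these numbers.

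**Statements side by side.**
- Secondary Outcomes text: uterine-sparing treatments only.
- Table 2, reintervention row: no restriction; rate by arm and by treatment; Cox comparison of the arms; complications of the initial treatment counted.
- Table 2, menopause and reproductive rows: the limit to uterus-saving treatments is written into the row titles. The reintervention row has no such wording.
- Table 1: reintervention is collected at 3, 6, 12 and 24 months and at data lock-in, with no treatment limit.
- Statistical Methods: intention-to-treat first.

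The first statement conflicts with the rest.

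**What the restriction would do if applied to the arm comparison.** Let h be the share of control women who have hysterectomy, and let rH, rU and rF be the 24-month reintervention rates after hysterectomy, after UAE or myomectomy, and after MR-HIFU.
- Control rate, all randomized women: h × rH + (1 − h) × rU
- Control rate, restricted: rU
- Inflation: rU / (h × rH + (1 − h) × rU), which equals 1/(1 − h) when rH = 0, the expectation in Strengths

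With rH = 0 the inflation is 1/0.90 = 1.11 at h = 10%, 1/0.75 = 1.33 at 25% and 1/0.50 = 2.00 at 50%.

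For the hazard ratio I assume rU = 10% and rF = 15% (neither is in the protocol) and approximate it as ln(1 − rF) / ln(1 − control rate). A value above 1 means more reinterventions after MR-HIFU. The restricted version gives ln(0.85)/ln(0.90) = 1.54 whatever h is. With all randomized women:

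| h (assumed) | Control women left of 80 if restricted | Control rate, rH = 0 | HR, rH = 0 | HR, rH = 5% | HR, rH = 15% |
|---|---|---|---|---|---|
| 10% | 72 | 9.0% | 1.72 | 1.63 | 1.47 |
| 25% | 60 | 7.5% | 2.08 | 1.77 | 1.36 |
| 50% | 40 | 5.0% | 3.17 | 2.08 | 1.22 |

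When rH is below rU, restriction moves the hazard ratio toward MR-HIFU (for example from 2.08 to 1.54). When rH is above rU, as in the last column, it moves the other way (for example from 1.36 to 1.54). When the two are equal, it makes no difference to these rates.

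**The case against.** The strongest reply is that the restriction was never meant for the arm comparison. The Secondary Outcomes sentence is an overview that points to Table 2, where the analysis is specified. The Table 2 row has no restriction, although the authors wrote one into the titles of two other rows. Table 1 and the intention-to-treat statement also point to all randomized women, and on that reading no bias arises. This stands. A reader might infer that the plan will drop hysterectomies and so flatter MR-HIFU, but the documents do not say that the arm-level rate or the Cox model uses the restricted set.

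The analysis set of a secondary Cox model is also often left to an analysis plan, and an article condenses its protocol. That would excuse silence. Here the article states an inclusion rule and then an analysis that contradicts it.

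Three further limits stand:
- Direction and size rest on assumed rates and an unknown hysterectomy share. Strengths expects most participants to prefer keeping the uterus, which points to the smaller shares.
- The Introduction and Strengths are only mildly in tension: an event can be unexpected without being ruled out.
- A reader might also infer that repeat surgery after hysterectomy would go missing from the cost-effectiveness analysis. The Primary Outcomes section does not support this. It costs additional in-hospital care during follow-up, and the management of complications, for all treatments. No passage says that the secondary reintervention rate feeds the lifetime model.

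**Conclusion.** The point holds as a contradiction in the stated analysis set, not as a demonstrated bias. The article contains two versions of the reintervention outcome. One compares the groups as randomized. The other, if carried into the arm comparison, removes control women by a choice made after allocation.

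On the protocol's own expectation of no reinterventions after hysterectomy, the second version inflates the control rate by 1/(1 − h) and favors MR-HIFU. The direction reverses if hysterectomy carries more reinterventions than UAE or myomectomy, which the documents give no figures to settle.

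The matter concerns a secondary outcome. The primary noninferiority test, the sample size and the cost-effectiveness analysis are not shown to be affected. It is still worth settling before outcome data are examined, because the trial is open and the comparator is chosen after allocation.

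**What to change.** In the Secondary Outcomes text, remove the uterine-sparing condition for the between-arm analyses. In the Table 2 row, state that the arm-level reintervention rate and the Cox model include all randomized women by allocated arm, that women who have a hysterectomy remain at risk, and that interventions for complications of hysterectomy count as the existing definition implies. Any result limited to uterine-sparing treatments can stay as a descriptive by-treatment result, labeled nonrandomized.

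The cost is a change of wording. Table 1 already collects reintervention from questionnaires and medical records without a treatment limit, so no new data, visits or participants are needed.

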### Data Collection

Data collection will take place before treatment, and at 3, 6, 12, and 24 months after treatment by questionnaires. Furthermore, baseline data of patient and treatment costs will be collected before treatment and after data lock-in (Table 1).

**Table 1 table1:** Timeline of data collection.

Data	Baseline	Treatment	3 months	6 months	12 months	24 months	Data lock-in
Informed consent	X						
Patient characteristics^a^	X						
Pregnancy outcomes^b^	X					X	
UFS-QoL^b,c^	X		X	X	X	X	
EQ-5D-5L^b,d^	X		X	X	X	X	
Onset of menopause^b^						X	
(Time to) reintervention^a^			X	X	X	X	X
Adverse events/complications^a^		X	X	X	X	X	
PREM^b,e^	X		X	X	X	X	
Recovery time^a^		X	X	X			
Medical Consumption Questionnaire^b,f^	X		X	X	X	X	
Productivity Costs Questionnaire^b,f^	X		X	X	X	X	
Costs of treatment^a^							X
Reason for not participating^a,g^	X						

^a^Retrieved from questionnaires and medical record.

^b^Retrieved from questionnaires solely.

^c^UFS-QoL: Uterine Fibroid Symptom and Quality of Life questionnaire.

^d^EQ-5D-5L: 5-level version of the EuroQoL Questionnaire.

^e^PREM: patient-reported experience measurement

^f^Used for the cost-effectiveness analysis.

^g^Data collected by the gynecologist in case of not willing to participate.

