### Sample Size

The MYCHOICE study is a noninferiority trial for which we hypothesize that MR-HIFU is noninferior to the group of standard (minimally) invasive treatments, accepted by a ≤15 points difference in symptom reduction at 24 months’ follow-up as determined with the SSS (range 0-100 points) part of the UFS-QoL questionnaire. We expect that women participating in this trial have a slight preference for the noninvasive MR-HIFU treatment. We therefore choose to use an unbalanced design in which participants are allocated to the intervention or usual care group at a 2:1 ratio, resulting in a larger sample size in the MR-HIFU treatment group. With a larger sample size of the MR-HIFU treatment group, we will be able to gather more data on this new treatment while the effectiveness of standard care is already much better documented. Randomization, stratified by center, will be performed using a computer-generated randomization system, which randomly selects block sizes of 3, 6, or 9. Previous studies concerning (minimally) invasive treatments were performed with women with an average baseline UFS-QoL SSS of 55-65 points [33]. Treatment initiated a decrease of 30-47 points on SSS 12 months after these combined treatments. Hitherto, there are 2 MR-HIFU studies published that used a full ablation protocol, had the same 12-month follow-up period as the studies on (minimally) invasive treatments, and in which women participated with a baseline UFS-QoL SSS of 55-65 points. These women showed an SSS reduction of 30-40 points at follow-up [34,35]. In our study population we expect comparable baseline SSS in the MR-HIFU and standard care group. However, because hysterectomy results in a somewhat higher SSS reduction than the uterus-saving treatments, we assume in our power calculation an a priori 5-point delta between both the MR-HIFU and standard care group in favor of the standard care group. Using a noninferiority margin of 15 points with α (1-sided)=0.025, β=.1, and an SD of 20 points, we estimate that 192 participants (128 patients in the MR-HIFU treatment group and 64 patients in the [minimally] invasive treatment group) will be required to test noninferiority of MR-HIFU. Anticipating a 20% loss to follow-up, we need to include 160 patients in the MR-HIFU group and 80 patients in the (minimally) invasive treatment group. The noninferiority margin and the SD of 20 points were determined in consultation with the Dutch Society for Obstetrics and Gynecology and were similar to the noninferiority margin used in the MYOMEX-2 study [36].

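### The 24-month reintervention rate is specified as a percentage that makes no allowance for incomplete follow-up, so the absolute and per-treatment risks can be off by an amount that depends on an unstated denominator

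*Protocol article*

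**What the plan says.** In the protocol article, Secondary Outcomes (Table 2, row on reintervention rate and time to reintervention), the 24-month rate "is presented as percentage reinterventions with its 95% CI". The same cell continues: "Reintervention rate will be presented per treatment arm but also per treatment". It then turns to the comparison of arms: "To investigate whether the time to reintervention differs between the 2 treatment arms, Cox proportional hazards analysis will be used".

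On how events are found, the row says: "Occurrence and type of reintervention are collected via both electronic patient file and questionnaires at 3-, 6-, 12-, and 24-month follow-up". Table 1 under Data Collection lists reintervention, with its timing, at 3, 6, 12 and 24 months and again at data lock-in. Its footnote gives the source: "Retrieved from questionnaires and medical record".

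Incomplete follow-up is expected. Sample Size has the phrase "Anticipating a 20% loss to follow-up", as the inflation step of the calculation for the symptom severity score (SSS). Statistical Methods adds three general rules:
- Women who withdraw before treatment or within 3 months stay in the database and are replaced.
- Women who withdraw later count as nonresponders.
- Once missing data reach 5%, the likely mechanism is examined and a suitable method is chosen.

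None of these rules says who is in the denominator of the reintervention percentage.

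**The concern.** A percentage of events needs a known 24-month status for everyone in its denominator. With incomplete follow-up there are three natural choices:
- **All women:** those lost early count as free of reintervention, so the rate is too low.
- **Women with known status** (an event, or 24 months completed): event-free dropouts leave the denominator, but events seen before a later dropout stay in, so the rate is too high.
- **Completers only:** about right if loss is independent of reintervention, but events in women who later left are discarded.

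The withdrawal rules add to the ambiguity. A woman who withdraws before treatment and is replaced would enter an all-women denominator as event-free with almost no observation. The term nonresponder has no stated meaning for reintervention.

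At stake are the absolute 24-month risk in each arm and the separate figures for MR-HIFU, embolization, myomectomy and hysterectomy. The Cox model compares the two arms through a hazard ratio and, as planned, supplies none of these. The Discussion (Strengths) calls reintervention rate the commonly used outcome in fibroid studies, so readers will look for these numbers.

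**Working it through.** **1. The plan's own figure, and what the 20% belongs to.** Inputs from Sample Size: "Using a noninferiority margin of 15 points with α (1-sided)=0.025, β=.1, and an SD of 20 points", an assumed 5-point difference in favour of standard care, and 2:1 allocation.
- Control n = (1 + 1/2) × [20 × (1.960 + 1.282) / (15 − 5)]² = 63.04, rounded up to 64. MR-HIFU n = 128. Total 192, as stated.
- 192/0.8 = 240, 128/0.8 = 160 and 64/0.8 = 80, as stated.

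The arithmetic is correct. The 20% is the loss allowance for a questionnaire endpoint, not a forecast of loss for reintervention.

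**2. Size of the bias at 20% loss.** The article gives no expected reintervention rate, so a true 24-month risk p = 20% is assumed here, with the range in step 3. Loss d = 20% is borrowed from Sample Size. Events and loss are independent with constant hazards, and no event is captured after loss. Over 24 months the cumulative hazards are H = −ln(1 − p) = 0.223 for events and L = −ln(1 − d) = 0.223 for loss.
- Observed events = H/(H + L) × [1 − (1 − p)(1 − d)] = 0.5 × (1 − 0.64) = 0.180. Over all women: **18.0%**.
- Known status = events + event-free completers = 0.180 + 0.8 × 0.8 = 0.820. Rate = 0.180/0.820 = **22.0%**.
- Completers: under independence the rate equals p, so **about 20%**.

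**3. Range over assumed event rates.** Simulation used 2,000,000 women per scenario, true risks of 5% to 30%, and constant or front-loaded event hazards. At 20% loss:

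| Denominator | Bias (points) |
|---|---|
| All women | about −0.4 to −2.9 |
| Known status | about +0.6 to +3.4 |
| Completers | about 0 |

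**4. If records cut loss to 5%.** With p = 20%, L = −ln(0.95) = 0.051.
- Events = 0.223/0.274 × (1 − 0.8 × 0.95) = 0.195, or 19.5% over all women.
- Known status: 0.195/(0.195 + 0.76) = 20.4%.

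Across true risks of 5% to 30% and both hazard shapes, the bias is at most about 0.8 points.

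**5. Set against sampling error.** The 95% CI half-width for a 20% rate is 1.96 × √(0.16/160) = 6.2 points with 160 women and 1.96 × √(0.16/128) = 6.9 points with 128.

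**6. Unequal loss, as a sensitivity case only.** Take equal true risks of 20% and assumed losses of 10% and 30%. The same formulas give 19.0% against 16.9% over all women, and 20.9% against 23.2% over known status. The apparent gap is about 2 points, and its direction depends on the denominator. For comparison, the half-width for a difference between 160 and 80 women is 1.96 × √(0.16/160 + 0.16/80) = 10.7 points.

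**The case against.** The strongest counter-case has five parts.

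- **The arms are compared by Cox regression.** Cox handles independent censoring, and the percentages are only presented. This stands. A reader might infer that the planned arm difference is biased. The protocol does not support that, because no test or estimate of a difference in percentages is planned. Two percentages side by side may still be read as a comparison, but that is a matter of presentation.
- **The 20% is not the loss for this outcome.** It comes from the SSS calculation, while reinterventions are also taken from the patient file and checked at data lock-in. This largely stands, and step 4 shows how far it shrinks the problem. Capture may be incomplete: MR-HIFU is given in only two hospitals to women referred from elsewhere, so an event could fall outside the file that is consulted. The article gives no figure for this.
- **Bias is not certain.** This stands too. A completers-only percentage is about unbiased under independent loss, so a flat statement that the rate is biased goes too far.
- **A Kaplan-Meier risk is also a percentage with a 95% CI, and the analysis plan may say so.** That is possible, and it keeps the point modest. The wording as it stands names an estimator that makes no allowance for follow-up, next to a time-to-event model that does.
- **The 5% missing-data rule covers it.** Only in general terms. The rule names no method and does not settle the denominator of this rate.

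A reader might also suppose that this percentage feeds the lifetime cost-effectiveness model. The article does not say so.

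**Conclusion.** The point holds as a modest improvement to a descriptive secondary outcome. As worded, the 24-month reintervention percentage takes no account of incomplete follow-up, and its bias depends on a denominator that is not stated. The shift is about 2 points either way at an assumed true risk of 20% with 20% independent loss and no record capture. It is about zero for completers, and under about 1 point if record retrieval brings loss down to about 5%. In the 20% example it is well inside the sampling error of a single arm.

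The sample size, the primary SSS analysis and the Cox comparison of arms are unaffected. The absolute and per-treatment 24-month risks are affected, because nothing else in the plan supplies them. The event rates, the 5% loss and the unequal losses are assumptions, since the article gives no values for them.

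**What to change.** In the reintervention row of Table 2, or in the analysis plan, replace the percentage with the 24-month reintervention risk estimated as a Kaplan-Meier cumulative incidence (1 minus the Kaplan-Meier estimate at 24 months) with 95% CI, per arm and per treatment. Censor each woman at her last contact or last record check, whichever is later, and keep the Cox model alongside. State how women who withdraw before treatment or within 3 months enter this analysis. If a plain percentage is also shown, name its denominator and give the number with known 24-month status in each group.

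The cost is a change of wording. Event and censoring dates are already needed for the Cox model, so no new data and no change in sample size are required. Kaplan-Meier, like Cox, assumes that loss is unrelated to reintervention. If women leave because of persisting symptoms, bias remains.
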